### Participant withdrawal criteria

(i.e. terminating investigational product/trial treatment) and procedures specifying:

*(a) when and how to withdraw participants from the project;*

Participants can ask to withdraw from this study at any time. To do so, they need to inform a member of the research team that no longer want to be involved. Contact details of the research team will be provided in the Participant Information Form. Withdrawal from the study would not mean a withdrawal of treatment. i.e., participants can still access usual care and no impact on any future BC treatment.

*(b) the type and timing of the data to be collected for withdrawn participant(s);*

We will ask any participant who chooses to withdraw from the study if we can retain any data already collected.

*(c) whether and how participants are to be replaced; and*

We will continue to recruit until the required sample size has completed the 16-week intervention period.

*(d) the follow-up for participants withdrawn from the project.*

Nil – other than usual care.

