## OTHER VARIABLES

**Descriptive variables** will be recorded such as age, sex, body mass index, employment status, co-morbid conditions, stage of cancer and details of cancer treatment.

**Healthcare utilisation and adherence with exercise** will be assessed in both groups. In the control group, this will be documented during the monthly phone calls and exercise diaries. In the experimental group, this will be monitored by asking each participant during the weekly supervised sessions and also using exercise diaries (see Section 4, Monitoring). Regarding healthcare utilisation, we will ask each participant to recall the number of; (i) visits to the Emergency Department, (ii) inpatient admission days, (ii) outpatient appointments and, (iii) visits to any other healthcare provider (Y/N, who, number of visits). Regarding adherence with exercise, we will ask each participant to recall the number of minutes spent engaging in moderate or vigorous intensity exercise and details regarding any resistance exercise.

**Absenteeism and presenteeism** will be assessed using the iMTA productivity cost questionnaire (Bouwman 2015).

**Global rating of change** will be assessed by asking participants, on completion of the SMART exercise program, to indicate if their health-related quality of life or exercise tolerance had 'improved', 'worsened' or 'stayed the same'. Those participants who rated their walking ability as 'improved' or 'worsened' will then be asked to rate the degree of change on a seven-point scale (1 a little better to 7 a great deal better).

**Feasibility and acceptability** will be measured using; (i) Quantitative data from an acceptability and feasibility questionnaire, and (ii) qualitative data from exit interviews. These are described below:

*Quantitative data* will be collected using a questionnaire asking participants to rate their perceptions of the SMART exercise program (e.g., "*I thought the SMART exercise program was easy to understand*"). Participants can rate each item on a five-point scale (1 "*I don't agree at all*" to 5 "*I totally agree*"). Four open-ended items at the end of this questionnaire allow participants to include additional feedback (e.g., "*What did you like about the SMART exercise program?*").

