*Qualitative data* will be collected using exit interviews upon completion of the SMART exercise program. Participants will have the opportunity to opt-in to semi-structured interviews to share more in-depth information about their experience with the SMART exercise program. Interviews will be conducted online and recorded using Teams, and are expected to last 30-45 minutes. Informed consent will be obtained from participants prior to the meeting and again before the interview or recording begins.

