## Efficacy assessment

Data collection will require two visits to the Physiotherapy Department at RPH. These assessments will be approximately 90 minutes in duration and will be completed pre-randomisation (baseline assessment) and at the end of the intervention phase. All other data collection will be done by extracting information from medical records, during phone conversations with the participants or by emailing out questionnaires through online formats (e.g. REDCap).

Table 1: Timing of outcomes

|                                                          | Pre-randomisation | Each week during the intervention phase | Mid-way through the intervention phase | On completion of the of intervention phase | 12 months following randomisation |
|----------------------------------------------------------|--------------------------|------------------------------------------------|-----------------------------------------------|---------------------------------------------------|------------------------------------------|
| Descriptive data (age, sex etc)                          | X                        |                                                |                                               |                                                   |                                          |
| EORTC QLQ C30 with BR45 (health-related quality of life) | X                        |                                                | X                                             | X                                                 | X                                        |
| EQ-5D-5L                                                 | X                        |                                                | X                                             | X                                                 | X                                        |
| Grip strength                                            | X                        |                                                |                                               | X                                                 |                                          |
| Deltoid, bicep and quads strength                        | X                        |                                                |                                               | X                                                 |                                          |

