| SRBAI                                                    | x                        |                                                | x                                             | x                                                 | x                                        |
| PANAS                                                    | x                        |                                                | x                                             | x                                                 | x                                        |
| Participation in exercise                                |                          | X                                              |                                               |                                                   |                                          |
| Healthcare utilisation                                   |                          | X                                              |                                               |                                                   |                                          |
| iMTA (absenteeism / presenteeism)                        |                          |                                                | X                                             | X                                                 | X                                        |
| Acceptability/ feasibility                               |                          |                                                |                                               | x                                                 |                                          |
| Exit interview                                           |                          |                                                |                                               | x                                                 |                                          |

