- What is the health care utilisation, absenteeism and presenteeism over the 12 months following randomisation?

This is an exploratory question and data will be described using mean and standard deviation.

*The third secondary research question is:*

- Does performance on tests of peripheral muscle force-generating capacity and exercise tolerance, change with test repetition (i.e. is there a learning effect)?

This will be assessed using one-way repeated measures analysis of variance (ANOVA). That is, for each participant, data collected over consecutive trials (5 attempts for each measure of muscle force and 2 attempts for the 6MWT) compared to explore if there is an effect of test repetition on these outcomes.

*The fourth secondary research question is:*

What is the minimal detectable difference in health-related quality of life and exercise tolerance?

This will be assessed using anchor-based approach via a Receiver Operating Characteristic curve. This curve will determine the optimal operating point to discriminate between participants who rate themselves as changed vs unchanged at the end of the SMART program.

*The fifth secondary research question is:*

Do psychological determinants of behavioural change, such as capability, opportunity, and motivation affect adherence to the SMART program and physical activity maintenance?

This will be assessed using correlations and a Multiple Regression Analysis of the data from psychological determinant measures (COM-B factors, impairment in functioning, intention, self-efficacy, habit, and mood) across all time-points for each participant. Data from the exit interviews will also be analysed using qualitative methods (such as thematic analysis) to explore participants' reasons for engagement (or lack of engagement).

*The sixth secondary research question is:*

Does the SMART program improve mood, and does mood influence adherence to the program and physical activity maintenance?

This will be assessed using correlations between mood data from the PANAS (across all timepoints) and physical activity engagement.

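### The acceptability questionnaire and exit interview are timed only at completion, and withdrawal ends follow-up, so SMART participants who leave early give neither

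*Protocol*

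**What the plan says.** Four parts of the protocol bear on this.

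- **Section 7, Other variables (Feasibility and acceptability).** The quantitative element "will be collected using a questionnaire asking participants to rate their perceptions of the SMART exercise program"; the text gives it no timing. The qualitative element "will be collected using exit interviews upon completion of the SMART exercise program". It is voluntary: "Participants will have the opportunity to opt-in to semi-structured interviews".
- **Section 7, Efficacy assessment, Table 1 (Timing of outcomes).** The rows "Acceptability/ feasibility" and "Exit interview" each carry a single mark, in the column "On completion of the of intervention phase".
- **Section 5, Participant withdrawal criteria.** The answers concern people who ask to leave the study. Under (b), they are asked whether data gathered so far may be kept. Under (d), follow-up is "Nil – other than usual care". No step records why a person left.
- **Section 9, Statistics and Interim Analysis, fifth secondary question.** Alongside correlations and multiple regression, exit-interview data will be analysed qualitatively "to explore participants' reasons for engagement (or lack of engagement").

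**The concern.** The interviews are meant to explain, among other things, why people did not engage. They are scheduled at the end, and withdrawal closes contact before that point. Someone who leaves in the early weeks because the program was too demanding or too inconvenient is among the best placed to say so, and the protocol provides no occasion to ask.

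Two results are at stake. Acceptability ratings would come from those still in the study at week 16 and could be read as describing everyone offered the program. The interview component of secondary question 5 would miss many of the least engaged. Analysis cannot repair this afterwards, because the data would never have been collected.

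**Working it through.** **Step 1. Follow three kinds of SMART participant through the schedule.**

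- *Takes part to week 16.* Text and table agree: questionnaire sent, interview offered.
- *Stops or largely skips sessions but stays in the study.* The questionnaire is timed only by Table 1, whose column is the end of the 16-week phase. Trial Duration/Schedule says all participants are reassessed then, so this person should receive it. For the interview, Table 1 points to the end of the phase, while the text requires completion of the program. This person reaches the first and arguably not the second, so eligibility is unclear.
- *Withdraws from the study before week 16.* Neither item has fallen due, follow-up is nil, and only data already held may be kept. There is no rating, interview or formal reason for leaving.

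The gap is definite for the third group and an ambiguity for the second.

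**Step 2. Size of the third group.** Inputs from Sample Size: difference 8, SD 20.52, alpha 0.05 (taken as two-sided, which reproduces the plan's figure), power 0.80, drop-out 20%.

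- n per arm = 2 × (1.960 + 0.842)² × 20.52² / 8² = 2 × 7.85 × 421.07 / 64 ≈ 103.3, rounded up to 104. This matches the protocol; power at 104 per arm is 0.803.
- Recruited per arm = 104 / (1 − 0.20) = 130, which also matches.
- Leavers in the SMART arm, if the allowance applied there: 0.20 × 130 = 26.
- Range if SMART drop-out were 10% to 30% (assumed): 0.10 × 130 = 13 to 0.30 × 130 = 39.

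**Step 3. Effect on an acceptability result.** Let *d* be the share who leave, *c* the proportion of stayers who find the program acceptable and *w* the proportion of leavers who would.

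- Whole-arm figure = (1 − d)c + dw.
- Overstatement from using stayers only = c − [(1 − d)c + dw] = d(c − w).

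The protocol gives neither *c* nor *w*, so these values are assumptions for illustration only. With d = 0.20, c = 0.90 and w = 0.40 to 0.60:

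- w = 0.40: 0.8 × 0.90 + 0.2 × 0.40 = 0.80, an overstatement of 10 points.
- w = 0.60: 0.8 × 0.90 + 0.2 × 0.60 = 0.84, an overstatement of 6 points.

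The direction holds whenever leavers rate the program lower than stayers; if they rate it alike, there is no bias.

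**The case against.** The strongest reply is that the schedule column is a calendar point that applies to everyone. A poorly adherent participant, or one who has stopped exercising but not left the study, is still assessed at week 16 and can explain a lack of engagement. This stands. A reader might infer that anyone who stops SMART is barred by rule and never asked, and the documents do not support that. The heading of the withdrawal section does mention ending trial treatment, but the answers beneath it are about leaving the study, and nothing says that stopping sessions triggers withdrawal. What remains for this group is the mismatch between program and phase.

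Other replies also limit the point:

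- Secondary question 5 rests mainly on quantitative measures taken at baseline, mid-way and later, with exercise participation recorded weekly. Data collected before withdrawal can be kept with permission. It would be wrong to infer that the question loses the non-adherent end of its range.
- Weekly sessions, side-effect questionnaires and adverse event records capture difficulties before a person leaves. This helps, but does not amount to an acceptability rating or a stated reason for leaving.
- The 20% is a planning allowance for the whole trial, and interviews are voluntary, so 26 is not a count of lost interviews.
- The instrument uses five-point items and open questions. No percentage-acceptable endpoint is defined, so Step 3 shows direction and plausible scale only.
- Risks and benefits links later implementation to exercise participation and sustained quality of life. It does not support the inference that acceptability ratings would drive that decision.

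None of these replies reaches the participant who withdraws before week 16.

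**Conclusion.** The point holds in a limited form. As written, SMART participants who withdraw before week 16 give no acceptability rating, interview or formal reason for leaving. That is up to about 26 of 130 if the 20% allowance applies to this arm, or 13 to 39 at an assumed 10% to 30%. For those who stop sessions but stay in the study, interview eligibility is unclear.

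Acceptability results would lean towards those who stayed, and the voluntary nature of the interviews may add to this. The interview part of secondary question 5 would miss many of the least engaged. The amount of bias cannot be derived from the protocol. The conclusion about its direction assumes that leavers view the program less favourably than stayers. The primary endpoint, the sample size and the quantitative part of question 5 are not materially affected.

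**What to change.** - **Feasibility and acceptability text, and Table 1 (Timing of outcomes):** offer both items to every participant allocated to SMART at week 16 regardless of adherence, or at study withdrawal if that comes first. Use the same trigger in both places.
- **Participant withdrawal criteria, (b) and (d):** add an optional, consented invitation at withdrawal to complete the questionnaire, give a reason for stopping and take part in an interview. Without this change, the nil follow-up rule would still block the contact.
- **Reporting:** give the number responding out of all allocated to SMART, and show results separately for those who finished and those who stopped, with the dividing line stated in advance.

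The cost is small. Questionnaires already go out electronically and interviews are held online, so the change needs no new visit and only one short additional item, the reason for stopping. It adds a few optional contacts. Some people who withdraw will decline, so the bias is reduced but not removed.

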## Efficacy assessment

Data collection will require two visits to the Physiotherapy Department at RPH. These assessments will be approximately 90 minutes in duration and will be completed pre-randomisation (baseline assessment) and at the end of the intervention phase. All other data collection will be done by extracting information from medical records, during phone conversations with the participants or by emailing out questionnaires through online formats (e.g. REDCap).

Table 1: Timing of outcomes

|                                                          | Pre-randomisation | Each week during the intervention phase | Mid-way through the intervention phase | On completion of the of intervention phase | 12 months following randomisation |
|----------------------------------------------------------|--------------------------|------------------------------------------------|-----------------------------------------------|---------------------------------------------------|------------------------------------------|
| Descriptive data (age, sex etc)                          | X                        |                                                |                                               |                                                   |                                          |
| EORTC QLQ C30 with BR45 (health-related quality of life) | X                        |                                                | X                                             | X                                                 | X                                        |
| EQ-5D-5L                                                 | X                        |                                                | X                                             | X                                                 | X                                        |
| Grip strength                                            | X                        |                                                |                                               | X                                                 |                                          |
| Deltoid, bicep and quads strength                        | X                        |                                                |                                               | X                                                 |                                          |
| 6MWT                                                     | X                        |                                                |                                               | X                                                 |                                          |
| Muscle mass                                              | X                        |                                                |                                               | X                                                 |                                          |
| Chemotherapy completion rates                            |                          | X                                              |                                               | X                                                 |                                          |
| COM                                                      | x                        |                                                | x                                             | x                                                 | x                                        |
| WSAS                                                     | x                        |                                                | x                                             | x                                                 | x                                        |
| Intention                                                | x                        |                                                | x                                             | x                                                 | x                                        |
| BTSES                                                    | x                        |                                                | x                                             | x                                                 | x                                        |
| HTQ                                                      | x                        |                                                | x                                             | x                                                 | x                                        |
| SRBAI                                                    | x                        |                                                | x                                             | x                                                 | x                                        |
| PANAS                                                    | x                        |                                                | x                                             | x                                                 | x                                        |
| Participation in exercise                                |                          | X                                              |                                               |                                                   |                                          |
| Healthcare utilisation                                   |                          | X                                              |                                               |                                                   |                                          |
| iMTA (absenteeism / presenteeism)                        |                          |                                                | X                                             | X                                                 | X                                        |
| Acceptability/ feasibility                               |                          |                                                |                                               | x                                                 |                                          |
| Exit interview                                           |                          |                                                |                                               | x                                                 |                                          |

